##### Participant engagement

At the end of the study, we will offer participants randomized to arm 2 and arm 3 the option to watch the intervention video (post-trial access to treatment) or end the study. The Gorilla platform will record this response and the time spent watching the video. The participants will be informed that they would not be compensated for the additional time taken to watch the intervention video.

#### Secondary outcome measures

Components of the complexity of vaccine hesitancy that have been identified in the research, namely COVID-19 risk and benefit perception, social norms, hope, and optimism, are secondary outcomes that we hypothesize will change as a result of the intervention. Therefore, all participants will be asked to complete questionnaires measuring their perceptions of severity and susceptibility, response efficacy, attitude, self-efficacy, social norms, as well as questions relating to optimism, hope, and trust.

##### Perceived severity and susceptibility

Perceived severity and susceptibility to COVID-19 vaccine will be assessed with three items adapted from Witte et al. (33) and Nabi and Myrick (34), each with three items on a 7-point Likert scale anchored by strongly disagree (1) and strongly agree (7). The three items for severity will be:

I believe that COVID-19 vaccine is severe.I believe that COVID-19 vaccine is serious.I believe that COVID-19 vaccine is significant.

The three susceptibility items will be as follows:

I am at risk for COVID-19.It is likely that I will get COVID-19.It is possible that I will get COVID-19.

##### Perceived response efficacy

Three items adapted from Witte et al. (33) and Nabi and Myrick (34) will assess perceived response efficacy. Possible responses will be arranged along a 5-point Likert scale, ranging from 1 (strongly disagree) to 5 (strongly agree).

Getting vaccinated against COVID-19 works in preventing COVID-19 disease.Getting vaccinated against COVID-19 is effective in preventing COVID-19 disease.If I get vaccinated against COVID-19, I am less likely to suffer from COVID-19 disease.

##### Attitude

Attitude toward COVID-19 vaccine will be assessed by asking participants to rate their agreement, from 1 (strongly disagree) to 7 (strongly agree), with two statements adapted from Nabi and Myrick (34):

I feel that getting vaccinated against COVID-19 is a wise thing to do.I think that getting vaccinated against COVID-19 is more trouble than it is worth (reverse-coded).

##### Perceived self-efficacy

To measure self-efficacy, which refers to a person's self-confidence in performing a desired behavior (35), participants will be asked to rate their agreement on a 7-point Likert scale, ranging from 1 (strongly disagree) to 7 (strongly agree). The following three items were adapted from Witte et al. (33) and Nabi and Myrick (34):

I am able to get vaccinated against COVID-19 to prevent COVID-19 disease.Getting vaccinated against COVID-19 to prevent COVID-19 disease is easy to do.Getting vaccinated against COVID-19 to prevent COVID-19 disease is convenient.

##### Perceived social norms

Four statements adapted from Quinn et al. (36) will be used to measure social norms, which comprise both perceived and observed regulations, as well as conventions and behaviors of others:

Descriptive norm (1 – few; 5 – nearly all).

1. How many of the people in the US do you think got the COVID-19 vaccine?

Subjective norm (1 – few; 5 – nearly all).

2. Of the people close to you, what proportion wants you to get the COVID-19 vaccine?

Moral norm (1 – not at all; 4 – very strongly).

3. It is my moral obligation to other people to get the COVID-19 vaccine.

Injunctive norm (1 – no expectation; 2 – encouraged; 3 – required).

What is the expectation at your workplace/school when it comes to the COVID-19 vaccine?

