### Participants

Participants must be over the age of 18 (male, female, or other), have a current address in the United States, and be proficient in English. Participants who do not meet the inclusion criteria will be excluded from the study. We will recruit study participants stratified by age and gender in order to replicate the age-sex distribution of the adult population in the United States, and vaccination status (no doses, one, two, three or more doses received; or tested COVID-19 positive).

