Our third objective is to determine whether study participants in the non-intervention arms are willing to voluntarily engage with the SAS video about the COVID-19 vaccine at the end of the study. The decision to view the SAS video and the duration of time spent watching the SAS video will be used to determine participant engagement. We will create a dummy variable that equals 1 when the participant clicks the “Play” button to view the SAS intervention video and 0 when the participant chooses to skip the SAS intervention video and click “Finish” the study to assess the participant's willingness to watch the SAS intervention video. We will employ a logistic approach to measure the sociodemographic parameters that influence the decision to watch or not watch the intervention video post-trial:

(3)
$$\begin{array}{r} WatchVideo_{i}=\gamma_{0}+\gamma_{1}VideoArm_{i}+\gamma_{2}X \end{array}$$

where *y*_*i*_ is a dummy variable which equals 1 when the participant clicks on the “Play” button to begin watching the SAS intervention video and 0 otherwise, *VideoArm*_*i*_ indicates the *k*th arm, *X* is a vector of covariates.

Among the participants who will choose to watch the SAS intervention video, we will quantify the length of time that they will spend watching the SAS intervention video using the timestamps provided by Gorilla's graphical experiment builder. We will use ordinary least squares (OLS) regression models to investigate which sociodemographic factors were associated with engagement time.

(4)
$$\begin{array}{r} EngagementTime_{i}={\text{λ}}_{0}+{\text{λ}}_{1}VideoArm_{i}+{\text{λ}}_{2}X \end{array}$$

where *EngagementTime*_*i*_ is the length of time participant *i* spent watching the SAS intervention video reported in seconds (min = 0, max = 1,800), *VideoArm*_*i*_ indicates the *k*th arm, *X* is a vector of covariates.

Regarding our second objective, we will explore the differences in individual factors related to the levels of vaccine hesitancy between the vaccinated and unvaccinated study participants. To do so, we will first compute a comprehensive score for each individual factor which are: perception of risk and benefit, attitude, self-efficacy, perceived social norms, and trust. We will then inspect correlations between such factors and participants' vaccination status using OLS models.

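### The injunctive-norm item, as printed, has no answer for adults without a workplace or school, which can distort the social-norms score in the exploratory comparison by vaccination status

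*Protocol article*

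**What the plan says.** Under Perceived social norms, the protocol article says: "Four statements adapted from Quinn et al. (36) will be used to measure social norms". The fourth item reads "What is the expectation at your workplace/school when it comes to the COVID-19 vaccine", with the response set given as "Injunctive norm (1 – no expectation; 2 – encouraged; 3 – required". Every point on that scale carries a label. The other three items run 1-5 (descriptive), 1-5 (subjective) and 1-4 (moral).

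Under Participants, eligibility is stated as: "Participants must be over the age of 18 (male, female, or other), have a current address in the United States, and be proficient in English". Recruitment is stratified by age and gender "in order to replicate the age-sex distribution of the adult population in the United States", and also by vaccination status.

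Under Statistical methods for primary and secondary outcomes, the plan is: "we will first compute a comprehensive score for each individual factor which are: perception of risk and benefit, attitude, self-efficacy, perceived social norms, and trust". It continues: "We will then inspect correlations between such factors and participants' vaccination status using OLS models". No covariates are named for these models, whereas the two engagement models in the same section carry a covariate vector. The rule that a missing answer scores zero is stated for the knowledge score only.

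**The concern.** The question presupposes a workplace or school. A sample recruited to the US adult age distribution will contain retired people, and nothing in the eligibility criteria keeps out unemployed or home-based adults. As printed, such a person has two choices:

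- Answer 1. The code then means either that the employer expects nothing or that there is no employer.
- Leave the item blank. A sum score then falls, a complete-case score drops the person, and a mean of the answered items shifts because the item ranges differ.

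Whether someone has a workplace or school depends on age and employment, and both may also relate to vaccination status. An unadjusted association between the social-norms score and vaccination status could then partly reflect who is employed rather than what norms people perceive. At stake is the reading of one exploratory secondary association. No primary outcome, sample size or error rate depends on the item.

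**Working it through.** The article gives no figure for this item, so there is nothing to reproduce. The check asks what the printed scale can do to the score under stated assumptions.

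**Inputs from the article.** There are four items with ranges 1-5, 1-5, 1-4 and 1-3. A plain sum therefore runs from 1+1+1+1 = 4 to 5+5+4+3 = 17. The article does not say whether the score is a sum or a mean.

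**Assumed inputs.**
- q, the share without a workplace or school: 20% to 50% in each group.
- m, the mean answer among those who have one: 1.5 to 2.5.
- Everyone without either answers 1.

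**Shift within one group.** The observed item mean is (1-q)m + q, so the sum score shifts by -(m-1)q.
- Smallest: m = 1.5, q = 20% gives -0.5 × 0.20 = -0.10.
- Largest: m = 2.5, q = 50% gives -1.5 × 0.50 = -0.75.

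**Shift in the vaccinated-minus-unvaccinated difference, same m in both groups.** This is -(m-1)(q_vacc - q_unvacc).

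| m | q vaccinated | q unvaccinated | Shift in difference |
|---|---|---|---|
| 2.0 | 30% | 30% | 0 |
| 2.0 | 40% | 30% | -0.10 |
| 2.0 | 30% | 40% | +0.10 |
| 2.0 | 50% | 20% | -0.30 |
| 2.0 | 20% | 50% | +0.30 |
| 2.5 | 50% | 20% | -0.45 |
| 2.5 | 20% | 50% | +0.45 |

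**Equal shares, but a real difference in m (2.2 against 1.8).** The item difference of 0.40 shrinks to 0.40(1-q): 0.32 at 20%, 0.28 at 30% and 0.24 at 40%.

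**Scoring from the remaining three items without rescaling.** Take a person at every midpoint: 3, 3, 2.5 and 2.
- Sum: 10.5 with all four items and 8.5 with three. A 10-point difference in shares then shifts the group difference by 0.10 × (-2) = -0.20. The coding problem itself gives -0.10 at m = 2.0.
- Mean: 10.5/4 = 2.625 with four items and 8.5/3 = 2.833 with three. The same 10-point difference gives 0.10 × 0.208 = +0.021, against -0.10/4 = -0.025 for the coding problem.

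Dropping the item only for those to whom it does not apply, on the raw scales, therefore swaps one artefact for another of similar or larger size. On a 0-1 scale, (x - min)/(max - min), the same person scores 0.5 on every item and 0.5 on average, whether three or four items are used.

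**The case against.** The strongest case against has four parts.

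1. **Bias is possible, not shown.** A reader might infer that the score is falsely low for these people and that the comparison is biased. The documents do not support that. Some may skip the item or answer for a former or household workplace. For a person with no workplace, 'no expectation' can be literally true. The working shows that the shift can be zero or of either sign. This objection stands.

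2. **A false significant result does not follow.** With shares of 35% and 25% and a mean of 2.0 elsewhere, the item means become 1.65 and 1.75. Groups of 8,910 and 1,090 with an item SD of 0.8 give SE = 0.8 × √(1/8,910 + 1/1,090) = 0.0257 and z = 0.10/0.0257 = 3.9. But that z belongs to the single item, while the plan analyses a composite. If a four-item sum had an SD of 2 to 3 (assumed), the same shift would give z of about 1.6 to 1.0. The 10.9% behind the group sizes is, in the Introduction, the share of US adults still hesitant, not the share unvaccinated. Recruitment is also stratified by vaccination status. This objection stands.

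3. **The affected contrast is exploratory and not randomised.** Age and employment can confound it however the item is coded. Between the trial arms, which is how the Introduction words the secondary objective, randomisation balances the inapplicable share in expectation. That comparison loses some sensitivity at most. This objection stands.

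4. **The full questionnaire may hold a skip or not-applicable option that a condensed article omits.** That may be so. The point rests, however, on a closed and fully labelled response set that the article does print. If a further option exists, one phrase in that section settles it.

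**Conclusion.** The point holds as a minor measurement flaw. The printed response set gives no answer to people whom the eligibility and recruitment rules bring in, and the item feeds a score that is related to vaccination status with no covariates named. Merging 'not applicable' with 'no expectation', or leaving blanks with no stated rule for this score, can distort that exploratory association.

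Size and direction are unknown. The illustrative range of -0.45 to +0.45 points on a 4-to-17 sum rests on three assumptions: shares of 20% to 50%, a mean of up to 2.5 among those with a workplace or school (the same in both groups), and everyone else answering 1. The documents do not support a claim that the score is wrong, that the comparison is biased in a known direction, or that the randomised arm comparison is biased in this way.

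**What to change.** Add a fourth response, 'I do not currently have a workplace or school', and treat it as not applicable rather than as a scale point. Analyse the injunctive item only among those to whom it applies.

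For the social-norms score, state one of two rules:
- use the descriptive, subjective and moral items for everyone; or
- rescale each item to a common range, for example 0-1, and average over the items that apply.

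The first keeps the same content for all participants. The second keeps the injunctive item but can still shift slightly if its rescaled mean differs from that of the other three items. Dropping the item for some participants on the raw scales should be avoided, for the reason shown in the working.

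The cost is one response option, one scoring rule and a smaller group for the injunctive item. The study timeline already includes a revision step after the pilot, which is a natural point to make the change.

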##### The adult hope scale

We will use the Adult Hope Scale to evaluate hope. The scale measures a person's level of hope according to Snyder's definition of hope as “a positive motivational state that is based on an interactively derived sense of successful (a) agency (goal-directed energy), and (b) pathways (planning to meet goals)” (37). The scale consists of 12 items, each measured using a 8-point Likert scale (1 = Definitely False; 2 = Mostly False; 3= Somewhat False; 4 = Slightly False; 5 = Slightly True; 6 = Somewhat True; 7 = Mostly True; 8 = Definitely True):

I can think of many ways to get out of a jam.I energetically pursue my goals.I feel tired most of the time.There are lots of ways around any problem.I am easily downed in an argument.I can think of many ways to get the things in life that are important to me.I worry about my health.Even when others get discouraged, I know I can find a way to solve the problem.My past experiences have prepared me well for my future.I've been pretty successful in life.I usually find myself worrying about something.I meet the goals that I set for myself.

Of the 12 items, 4 make up the Agency sub-scale (2, 10, 11, 13) and 4 make up the Pathways sub-scale (1, 4, 6, 8). The remaining 4 items are fillers.

##### Optimism

Optimism will be quantified using the validated scale of Brandtstädter and Wentura (38). The following five items will be rated on a 4-point Likert scale (1=strongly disagree, 4=strongly agree):

I am looking forward to the life ahead of me.For me the future is full of hope.Thinking about my future makes me worry.I look to the future with confidence.The future holds a lot of good in store for me.

##### Trust

Following Schmelz and Bowles' model (39), participants will be asked to rate their degree of trust in the (i) federal government, (ii) state government, (iii) experts from science, (iv) media, (v) medical professionals, and (vi) their social circle (family, friends, and colleagues) on a scale of 1 to 7 (1 = no confidence at all, 7 = a great deal of confidence).

Additionally, individuals will be asked to rate the degree to which they believe their country's government has been truthful about the coronavirus outbreak (1 = very untruthful, 5 = very truthful).

##### Follow-up with study participants

We will follow up with participants in a range of 4–8 weeks after the intervention to determine retention of COVID-19 vaccine knowledge, behavioral intent toward COVID-19 vaccination, and intrinsic interest in watching and sharing a SAS video about COVID-19 vaccine, by asking study participants:

Since your initial participation in this study, have you gotten the COVID-19 vaccine?Have you received another vaccine after your initial participation in this study?a. If yes, did the short-animated animation influence your decision to receive a vaccination?b. If not, please explain why did not get a vaccination?

3. Have you shared the short-animated video with others?a. If yes, with whom?b. If no, why not?

4. Have you discussed what you have learned in this study with others?a. If yes, what topics of this study did you discuss with others?b. If yes, who did you discuss with?c. If no, please explain why you did not discuss what you have learned in this study with others?

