**Figure 1 F1:**
[figure not shown]
Design of randomized controlled trials (second randomization is for a list experiment rather than for the group assignment). The order of the attention, knowledge, hope, and optimism questionnaires is sequential, since study participants complete them in succession. Inclusion criteria: Participants must be over the age of 18 (male, female, or other), have a current address in the United States, and be proficient in English.

After watching the video, participants will be asked to complete one attention question, four true/false knowledge questions about the COVID-19 vaccine, 14 Likert scaled questions about COVID-19 vaccine perceived risks and benefits, attitude, self-efficacy, and perceived norms, and 11 additional Likert scaled items indicating their level of hope and optimism. All questionnaires incorporating Likert scaled items were obtained from our prior research and are cited in the following sections that discuss the questionnaire items.

Furthermore, participants in each arm will be asked to complete five list experiments (25). For each list experiment, we randomized participants 1:1 to a control list or a treatment list. The control list consists of a list of four items about behavioral intent, which are unrelated to the COVID-19 vaccine. The treatment list consists of the same four list items as the control group, as well as a sensitive item assessing behavioral intent to get vaccinated and obtain additional information about COVID-19 vaccinations. The list experiment will be employed to decrease social desirability bias, as participants may already be primed to respond positively to questions about COVID-19 vaccines. Following completion of the list experiment, study participants will respond to seven questions regarding their level of trust in governmental bodies, institutions, and health care providers.

Study participants randomized to the APC group (arm 2) or the control group (arm 3) will be given the option to watch the COVID-19 vaccination intervention video as a post-trial access to treatment at the end of the experiment. The participants will be informed that they will not receive compensation for the time spent watching the SAS videos.

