### Strengths and limitations

This study will use an RCT design to assign individuals to watch a collage of three SAS videos about COVID-19 vaccine (arm 1), an APC video (arm 2), or no video (arm 3). The videos in arm 1 and arm 2 are identical in length (~4 min each) and similar in style. The randomization to the three trial arms will reduce the likelihood that systematic differences in groups may influence outcomes and will let us isolate the true effect of the SAS intervention videos.

The inclusion of the APC video is a novel component of our study that will allow us to quantify the content effect of the intervention. We define the difference between the SAS intervention videos and the control as the total effect, the difference between the SAS intervention videos and the APC video as the content effect, and the difference between the APC video and the control as the attention effect. There have been several entertainment-education studies that have employed an experimental approach to assess the effect of an intervention video in this way (47–51), but only few on COVID-19 (44, 45, 52).

In each of the three arms, we will run a list experiment to measure behavioral intent while eliminating social desirability bias. It is likely that participants will already be primed to give socially acceptable responses to questions about their views on the COVID-19 vaccine. The indirect questions (i.e., how many statements do you agree with) provide protection to participants if they want to reject the vaccine message without revealing this intention. To the best of our knowledge, few studies have employed a list experiment approach to assess the efficacy of an entertainment-education video in improving a specified health outcome (51, 52). Hence, we are aware that during the study our strategy could prove to have unforeseen disadvantages. Moreover, list experiments are focused on short-term effects of the intervention, which leaves us with uncertainty regarding the question if a SAS video would actually lead participants to get vaccinated in the near future.

Another objective is assessing participants' voluntary engagement with the SAS videos among participants assigned to the APC and control arms (post-trial access to treatment). The findings of this study will assist us in evaluating participants' willingness to watch online SAS videos, particularly when this willingness is weighed against a time cost, simulating a real-world scenario.

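### The 4–8 week follow-up is meant to determine retention of knowledge and intent, but none of its listed questions measures either

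*Protocol article*

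**What the plan says.** Under Follow-up with study participants, the protocol article fixes the timing: "We will follow up with participants in a range of 4–8 weeks after the intervention". It gives the purpose as "to determine retention of COVID-19 vaccine knowledge, behavioral intent toward COVID-19 vaccination, and intrinsic interest in watching and sharing a SAS video". The sentence then leads straight into the questions that are to serve this purpose. The four main ones are:

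1. "Since your initial participation in this study, have you gotten the COVID-19 vaccine"
2. "Have you received another vaccine after your initial participation in this study"
3. "Have you shared the short-animated video with others"
4. "Have you discussed what you have learned in this study with others"

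Seven sub-questions follow. Two belong to question 2 (whether the animation influenced the decision, or why no vaccine was received), two to question 3 (with whom the video was shared, or why not) and three to question 4 (topics, persons, or why not).

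Elsewhere the article defines the constructs precisely. Knowledge is a 0–24 score of correct true/false answers (Knowledge, Parts 1 to 3; Data analysis). Behavioral intent is a commitment over the coming two weeks (Outcomes), measured by five list experiments (Behavioral intent, Table 1). Interest in watching is the choice to play the video or finish, plus viewing time, in arms 2 and 3 (Participant engagement).

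On timing, Trial design (text after Figure 1) says that arms 2 and 3 "will be given the option to watch the COVID-19 vaccination intervention video as a post-trial access to treatment at the end of the experiment". That is the end of the first session, before the follow-up contact.

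**The concern.** The purpose and the instrument sit in one sentence and do not match. To report how much of a knowledge gain, or of a shift in intent, survives to 4–8 weeks, the trial must measure the same thing at both times. If the follow-up is fielded as written, the team will have no knowledge score and no intent estimate at the second time point, and a stated aim will go unanswered. There is also a risk that vaccine receipt and discussion are later reported as if they were retained intent and retained knowledge, which they are not.

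A lesser matter is how follow-up results by arm should be read. Participants in the two comparison arms have by then been offered the intervention video, so such a contrast is not simply exposed against unexposed.

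**Working it through.** No sample size or power figure enters this point, so there is nothing of that kind to reproduce. The check sets the follow-up questions against the article's own measures.

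**Knowledge.** The score runs over 12 items in Part 1, 2 in Part 2 and 10 in Part 3: 12 + 2 + 10 = 24, which agrees with the stated range of 0–24. Items repeated at follow-up: 0 of 24. The nearest question is the sub-question on topics discussed. It has no right or wrong answer, is not scored, and is put only to those who say they discussed the study.

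**Intent.** Five lists in the first session; lists repeated at follow-up: 0 of 5. The nearest questions are the two on vaccine receipt. They differ from the intent measure in three ways:
- They ask about what has already happened since the first session, whereas intent as defined looks forward two weeks.
- Receipt corresponds to one of the five sensitive items (getting the needed dose). Reading official information, talking to a health worker and learning about risks and benefits have no counterpart. Sharing official information is only loosely matched by the question on sharing the video.
- A list experiment yields a group-level proportion, from the mean difference between treatment and control lists. A yes/no answer on receipt is not on the same footing, so the two cannot be subtracted to give retention.

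**Interest in watching and sharing.** Sharing is asked directly. Interest in watching is not asked.

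**Tally of the four main questions.** Knowledge 0, intent 0, interest in watching 0, vaccine receipt 2, sharing 1, discussion 1.

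**Order of events.** First-session questionnaires and list experiments come first, then the offer of the intervention video to arms 2 and 3, then follow-up at 4–8 weeks. Everything measured in the first session therefore precedes the offer, and everything measured at follow-up comes after it. Participant engagement says that the choice and the viewing time are recorded, so the extent of viewing in arms 2 and 3 will be known.

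**The case against.** The best defence is that a journal article condenses a fuller document and that the complete follow-up questionnaire may be there. That would answer a silence, but the article is not silent: it names the aim, says it is met by asking these questions, and lists them with their sub-questions. What is stated does not fit, and nothing elsewhere in the article repairs it.

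A second defence is that actual vaccination is worth more than intent, and that discussion shows something was learned. Vaccination is indeed of interest in its own right. That supports keeping the questions; it does not make them a measure of retained intent or knowledge.

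A third defence concerns weight, and it stands. Follow-up measures are not among the named primary or secondary outcomes, no sample size rests on them, and the first-session outcomes are collected before the video is offered. The mismatch affects an ancillary aim.

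A reader might infer something stronger: that the follow-up vaccination result is contaminated and diluted by a calculable amount. The article does not support that. It states no between-arm analysis of follow-up data and no power for one. It gives no expected share of viewers in arms 2 and 3. Nothing shows that voluntary, unpaid viewing of variable length has the same effect as arm 1's viewing, which cannot be paused or skipped. The offer is also deliberate, since it supplies the third primary outcome. Strengths and limitations concedes "uncertainty regarding the question if a SAS video would actually lead participants to get vaccinated in the near future", so the article does not claim to settle the effect on vaccination. What remains is a caveat on interpretation.

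**Conclusion.** The point holds for knowledge and intent. As written, the follow-up repeats 0 of 24 knowledge items and 0 of 5 intent lists, so retention of either cannot be computed. Interest in watching also has no item. It would be too broad to say that the whole follow-up aim fails: sharing is covered, and vaccination, sharing and discussion are each usable as self-reported behaviours.

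The conclusion rests on taking the listed questions as the follow-up instrument, which is how the article presents them. It needs no numerical assumption.

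The timing of the video offer is a caveat and not a second defect. It bears on how any by-arm follow-up result is read, and no size can be put on it from the document. The first-session primary and secondary outcomes are untouched. The mismatch should be corrected before follow-up begins, because the missing measurements cannot be recovered afterwards.

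**What to change.** Choose one of two changes.

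- **Keep the aim.** Repeat the 24 knowledge items and an intent measure at the contact already planned, and add an item on interest in watching if that part of the aim is kept. For intent, the same lists are needed if change since the first session is to be reported; a new direct question would give only a level at follow-up, because the first session measures intent by lists alone. The cost is a few more survey minutes and the payment for them.
- **Keep the questions.** Restate the aim as self-reported vaccination, sharing and discussion at 4–8 weeks, and drop retention of knowledge and intent and interest in watching. The cost is wording only.

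Under either option, add a short statement that any follow-up comparison by arm comes after arms 2 and 3 were offered the intervention video. Report the share of each of those arms who watched it, which the platform already records. Do not present watchers against non-watchers as a randomised contrast, since viewing is self-selected. This matters more under the first option, because repeated knowledge and intent measures would also come after the offer.
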